#### Secondary outcomes

Secondary outcomes are: 1) the impact of the game-based appointment system on how the users utilise the web app www.sjekkdeg.no; 2) the potential benefit for health professionals (doctors and nurses) from such a system through reduced consultation times due to previously acquired information by the symptom checker; and 3) the potential benefit for the users from this game-based appointment system by reducing the booking time threshold of a consultation at the venereology department at the hospital.

On the impact of the game-based appointment system on how the users utilise the web app www.sjekkdeg.no, we expect that the number of visits to the educative components of sjekkdeg.no will increase, after the implementation of the game-based appointment system functionality. And also, we expect that the number of visits to the educative components of sjekkdeg.no will be higher in the appointment group when compared to the control group.

To assess if the game-based appointment system increases the number of visits to the educative components of the web app www.sjekkdeg.no, we will analyse and compare the absolute number and percentage of visits (new visitors and returning visitors) of users in Group A versus Group B after one year of the start of the project. The total number of visitors, as well as the number of new and returning visitors, included in both randomization groups, using the web app, and all of its components, will be tracked through the web analytics tool Google Analytics.

Regarding the potential benefit for health professionals (doctors and nurses) from such a system; we expect that health professionals will be satisfied by having reduced consultation times due to previously acquired information by the symptom checker. To assess if health professionals (doctors and nurses) can benefit from such a system (e.g. through reduced consultation times), a qualitative approach consisting of an *ad hoc* questionnaire based on the Technology Acceptance Model [20], will be used.

On the potential benefit for the web app users; we expect that the time spent per visit to the web app will be longer in the appointment group than in the control group, implying a higher exposure to health information. And we also expect that the visitors’ returning rate will be higher in the appointment group when compared to the control group. To assess whether the game-based appointment system influences how the users utilise the web app www.sjekkdeg.no, we will compare, after one year of implementation, how much time the users spent on the web app, and on each educative component. To assess if the users can benefit from the game-based appointment system and how this functionality helped them in the decision to book an appointment with the doctor, a qualitative approach, consisting of an *adhoc* questionnaire based on the Technology Acceptance Model [20], will be used. The questionnaire will be available at the venereology unit, before the consultation.

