## Methods/Design

### Trial design

To assess the impact of the game-based appointment system, an A/B testing methodology is used. Two versions of the web app, www.sjekkdeg.no, will be used for the A/B test to explore the user interactivity with the site. Version A (control), consisting of the educative web app only; and Version B, which will additionally include a game-based appointment system. Users will be randomly selected to use one of the two versions of the web app. Thus, we will be able to assess which version better supports the typical user in tasks such as booking an appointment at the hospital venereology unit.

The novel game-based appointment system is integrated in the already existing web app www.sjekkdeg.no [10], a game-style web app on sexual health education including social media, targeting North-Norwegian youth, accessible through laptops, smartphones and tablet computers [10]. Gamification techniques [19] such as avatars, achievement-based gifts and social network sharing buttons have been implemented in www.sjekkdeg.no. The web app, which was launched at the end of 2012, seems to be a promising way to encourage users to learn more about sexual health, judging from preliminary visitor returning rates, the average pages visited and the time spent on it [19]. The data also show that the symptom checker is one of the most visited components of the web app [19].

The new game-based appointment system, made available to the users that have been randomized to the intervention group, is based on an automatic prioritization algorithm, which provides the opportunity to book an appointment online. Once randomized to the intervention group, a virtual doctor will ask questions concerning the symptoms that the avatar has experienced. According to the avatar’s answers, the virtual doctor suggests a possible diagnosis or, if a diagnosis is not possible, that the avatar should attend the clinic to be tested for STDs. The appointment system service will be available 24/7, from 1^st^ January 2015 until 31^st^ December 2015.

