The system was reviewed by a panel of specialists in venereal diseases. They contributed in the definition of the relevant symptoms that influence the priority attributed to the patients by the system. We envisaged three levels of prioritization (i.e. triage): 1) Emergency appointments: The user should see a doctor on the same day or the following day. Patients having fever or other signs of serious infection are assigned to this category. They are strongly advised to call the clinic by phone and should not use the game-based appointment system. 2) Haste-appointments: The user should see a doctor within 3-4 days. Typical cases are acute infections with itch or pain. 3) Routine-appointments: The user should see a doctor within 2-3 weeks. Most cases in this category are asymptomatic infections.

To book an online appointment the user will require a reference number that will appear jointly with the guided diagnosis provided in the symptom checker. Example of the user’s screen to book an appointment can be seen in Figure 1. This reference number will be the user’s “credentials” at the clinic. Simultaneously, the venereology unit will get an automatic notification with the provisional pre-selected day and time for the appointment, and the user’s symptoms report, which could be relevant for planning the workflow at the clinic. The appointment at the venereology unit is accepted by the health professionals once the user sends a SMS confirming his/her intention of showing up. Figure 2 shows the health professionals’ administration dashboard.

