**Study flowchart.**

All web app users, either belonging to Group A or Group B, that use the symptom checker functionality will receive individual advice, e.g. on infection prevention measures such as advice on how to use condoms until the applicant has tested him/herself for STDs or otherwise clarified his/her condition. The individual advice will be based on the information that the users have provided regarding their symptoms.

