### Intervention

The intervention group will be able to use a game-based appointment system in the web app, allowing them to book an appointment at the hospital venereology unit, in addition to all the educational content of sjekkdeg.no.

The control group will have access to the educative web app only.

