### Outcomes

#### Primary outcome

The primary outcome is the number of consultations with health professionals. We expect the number of visits with health professionals will be higher in the game-based appointment group (Group B) when compared to the control group (Group A).

To assess if the game-based appointment system increases the number of consultations on STDs at the venereology unit at the University Hospital of North Norway, we will analyse the total number of appointments booked through the web app within one year after implementation and compare this data with earlier appointments rates. We will compare the total number of STDs consultations belonging to Group A versus the total number of consultations attended through the game-based appointment-system (Group B) within one year of implementation (quantitative approach). To compare the total number of STDs consultations, users in the control group are asked to bring their symptom checker results including their randomization code, to the visit at the venereology unit. Attended visits at the venereology unit of users showing randomization codes belonging to the control group will be registered in a grid.

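### Total time per visit and overall visits are read as educational exposure, although booking, which only Group B can do, can raise both

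*Protocol article*

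**What the plan says.** Under Secondary outcomes, the protocol article lists potential benefits for users, among them this expectation about health information: "the time spent per visit to the web app will be longer in the appointment group than in the control group, implying a higher exposure". A higher returning rate in Group B is expected in the same place. The section also expects more visits to the educative components in Group B. It assesses this by comparing counts and percentages of visits by new and returning visitors, which are not limited to educative pages.

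The arms differ in what the app contains. The Intervention section gives Group B the booking system on top of all the educational content and says of Group A: "The control group will have access to the educative web app only". Booking has a prerequisite, stated under Trial design: "To book an online appointment the user will require a reference number that will appear jointly with the guided diagnosis provided in the symptom checker".

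The plan also contains a narrower comparison. Secondary outcomes and Statistical methods both compare the time spent on each educative component between the arms. The article does not define an educative component. It calls the symptom checker a component ("the symptom checker is one of the most visited components of the web app") without saying whether it is an educative one.

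**The concern.** A longer visit is evidence of more reading only if both arms spend their time on the same content. Here one arm has a task that the other cannot perform. Minutes spent choosing and requesting an appointment count towards time on the app, and a visit made only to book counts as a visit. Neither is health information. Because booking runs through the symptom checker, it can also raise checker use in Group B. If the checker is counted as educative, this carries over into the component-level measures.

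At stake is a secondary conclusion. The trial could report that the appointment system increases exposure to sexual health education when it has only shown that people who can book spend time booking. The primary outcome is not affected.

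**Working it through.** **Figures in the plan.** The article gives no time per visit, booking time or visit count by arm, so there is no figure to reproduce. The check has two parts: the text set side by side, and an illustration with assumed inputs.

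**The text side by side.**

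| Measure | Stated reading or use | Can booking raise it in Group B? |
|---|---|---|
| Total time per visit | Higher exposure to health information | Yes: booking steps, and checker time needed to book |
| Visits, new and returning | Visits to the educative components | Yes: a visit made to book counts in full |
| Returning rate | Listed with benefit for users | Yes: same reason |
| Time on each educative component | How users utilise the app | Not through booking pages, if these are not classed as educative; possibly through the checker, whose class is not stated |

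The measures that carry the exposure and educative-visit readings are the ones open to the artefact. The best protected measure, time by component, is not the one to which the exposure inference is attached.

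**Illustration; the time and booking inputs are assumptions.** Take 500 users per arm (the planned 1000, split 1:1), one visit each, no true difference in educational use, and an SD of visit time of 4 or 6 minutes. A share s of Group B visits carries m extra minutes for booking and the checker run that it requires. Statistical methods does not name total time per visit among the tested variables, so a two-sided t-test at 0.05 is also assumed.

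- Shift in mean time = s × m
- SD in B = √(SD² + s(1−s)m²); pooled SD = √((SD² + SD in B²)/2)
- SE = pooled SD × √(2/500)
- Chance of a significant excess in B = Φ(shift/SE − 1.96)

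Worked case with s = 0.3, m = 4, SD = 6: shift = 1.2; SD in B = √(36 + 0.21 × 16) = √39.36 = 6.27; pooled SD = √((36 + 39.36)/2) = √37.68 = 6.14; SE = 6.14 × 0.0632 = 0.388; 1.2/0.388 = 3.09; Φ(3.09 − 1.96) = 0.871.

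| Share s | Extra minutes m | Shift (min) | Chance, SD 6 | Chance, SD 4 |
|---|---|---|---|---|
| 0.1 | 2 | 0.2 | 7.6% | 12.0% |
| 0.1 | 4 | 0.4 | 18% | 34% |
| 0.3 | 2 | 0.6 | 35% | 65% |
| 0.3 | 4 | 1.2 | 87% | 99.5% |
| 0.5 | 2 | 1.0 | 74% | 97% |

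With no artefact, the chance in this direction would be 0.05/2 = 2.5%.

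**How common might booking be?** Sample size assumes that about 50%, or 30%, of Group A users attend, with detectable changes of 20% and 30% respectively. Read as relative increases, these give 0.50 × 1.20 = 60% and 0.30 × 1.30 = 39% of Group B users. The Primary outcome section counts Group B consultations as those attended through the booking system. On the trial's own planning, then, booking need not be rare. These are shares of users rather than visits, and with several visits per user the share of visits would be lower, so they cannot be put into the table directly.

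**The case against.** The strongest reply is that the protection is already planned. Time on each educative component is compared in both arms, and it is the time variable that Statistical methods names for testing; the quoted sentence only states an expectation. This stands in part. It means that the web-use results need not all favour Group B, since time on reading pages would show no difference if there were none. It does not remove the inference from total time, and it does not cover visits, which are assessed overall.

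A reader might go further and infer that symptom checker use rises in Group B by construction. The documents do not support this. The checker is open to both arms: "All web app users, either belonging to Group A or Group B, that use the symptom checker functionality will receive individual advice". Group A also has a study-driven reason to use it, because "users in the control group are asked to bring their symptom checker results including their randomization code, to the visit at the venereology unit". The difference is one of degree. The checker also gives prevention advice, so part of the time spent there is real exposure.

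A reader might likewise treat the virtual doctor as a second module that only Group B has, from the sentence "Once randomized to the intervention group, a virtual doctor will ask questions concerning the symptoms that the avatar has experienced". That dialogue may be the shared checker itself, because Trial design places the guided diagnosis in the checker. The booking step is the only content that is clearly exclusive to Group B.

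Nor does the sentence that begins "The total number of visitors, as well as the number of new and returning visitors, included in both randomization groups, using the web app, and" define a pooled outcome that includes booking pages. It describes what the analytics tool tracks, and tracking by component is what makes a separation possible.

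Finally, a list of educative pages may be in a fuller document. That would settle the classification, but not the inference, which the article states itself.

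**Conclusion.** The point holds as a matter of interpretation on secondary outcomes. Longer total time per visit and more overall visits in Group B would not by themselves show more use of educational content, because Group B alone has a booking task and that task passes through the symptom checker. The component-level comparison guards partly against a wrong conclusion.

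The size cannot be derived from the document. It depends on the share of visits that include booking and on the minutes that booking adds, and neither is given. Under the assumptions above, the artefact is small if booking is rare and short, and could by itself produce the expected result if booking is common.

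**What to change.** - State which components are educative, and base the educational-exposure conclusion on time and visits to the educative pages common to both arms, excluding the booking pages.
- Report the symptom checker separately, since both arms can use it and it gives some real advice.
- Report total time per visit and returning rate as descriptive measures of use, and delete the inference to higher exposure.

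Return visits need no new definition; it is enough not to read them as education. The component tracking already planned should supply the data. The cost is a filter in the analytics set-up, a reworded hypothesis and a less favourable reading of total time.

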### Sample size

The web app www.sjekkdeg.no has been running for more than one year and has had, so far, more than 800 unique visitors from Tromsø. We expect the use of the web app to increase further, as it gradually becomes more known. This allows us to assume that one year will be enough to conduct the study and have 1000 visitors.

If 1000 www.sjekkdeg.no users are randomized into the two groups, Group A and Group B, and approximately half of the users in Group A attend an appointment, we can detect a 20% change in the appointment rate (with beta = 0,80 and alpha = 0,05). If the number of appointments attended by users in Group A is lower than expected, the difference between the groups must be larger for us to detect it. With a 30% attended appointments rate in Group A, we still have power to detect a 30% difference between the groups (with beta = 0,80 and alpha = 0,05).

### Interim analysis and stopping guidelines

Because of the educational nature of the research study, no interim analysis or stopping guidelines are planned.

### Randomisation

The users from Tromsø will be randomized either to the Group A, or to Group B, with a 1:1 allocation ratio (See the study flowchart in Figure 3). Simple randomization will be used. The random allocation sequence will be generated automatically using Google Analytics randomizer code.

Web app users and health professionals are not blinded.

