**Figure 2 Fig2:**
[figure not shown]
**Health professionals’ administration dashboard.** Screen capture from www.sjekkdeg.no administration dashboard.

The appointment system is designed to preserve the user’s anonymity. Thus, users will not need to provide their name or other personal data to use the appointment system. Only the health professionals at the venereology unit, at the University Hospital of North Norway, will be able to identify patients before their appointments through their cell phone numbers.

The users who ask an appointment through the web app, and who come to the visit at the venereology unit will be asked to sign an informed consent.

To our knowledge, a sexual health web-based app with this type of functionality has not been reported in the literature.

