### Participants

The web app www.sjekkdeg.no is of free use, and accessible to everyone, although only the users from the city of Tromsø are eligible to participate in this study.

Once a user accesses the web app www.sjekkdeg.no, an informed consent appears on the screen. If the user agrees to participate in the research project, then, a question asking his/her location will appear, as follows: “All the content on this web app is completely anonymous. For research purposes, we only would like to know if you are from Tromsø.” There are two possible answer-options: “Yes, I am from Tromsø”; or “No, I am not from Tromsø”. Users selecting the option “No, I am not from Tromsø” will be immediately selected for the Group A or control group (i.e., the educative web app, without the game-based appointment system). Users answering, “Yes, I am from Tromsø” will be randomized either to the Group A, or to Group B (educative web app, including the game-based appointment system), with a 1:1 allocation ratio (See the study flowchart in Figure 3).

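### One person may be allocated more than once, and the counting rule can then move some first-allocated control attenders into Group B

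*Protocol article*

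**What the plan says.** All references are to the protocol article.

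- **Trigger for allocation.** Participants: "Once a user accesses the web app www.sjekkdeg.no, an informed consent appears on the screen". A user who consents and says that he or she is from Tromsø is then randomised 1:1.
- **Mechanism.** Randomisation: "The random allocation sequence will be generated automatically using Google Analytics randomizer code". The article does not say what this code recognises (a person, a browser or a visit) or how long an allocation lasts.
- **Devices and duration.** Trial design describes the app as "accessible through laptops, smartphones and tablet computers" and runs the booking service for the whole of 2015.
- **Anonymity.** Later in the same section: "users will not need to provide their name or other personal data to use the appointment system". Clinic staff can, however, identify patients by cell phone number before their appointments.
- **Counting.** Primary outcome sets Group A consultations against consultations attended by way of the appointment system, which stand for Group B. Control users are asked to bring their symptom-checker results with the randomisation code. Their visits are entered in a grid when a control code is shown.
- **Unit.** Sample size moves from a forecast of 1000 visitors to "If 1000 www.sjekkdeg.no users are randomized into the two groups, Group A and Group B".

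The article gives no rule for a person who has received both versions or holds a code from each.

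**The concern.** Two features combine. First, allocation is attached to access to the site, and the article describes no account or other link that would recognise the same person on a phone and later on a laptop. A second consent and a second 1:1 draw are therefore possible.

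Second, the two arms are counted by different rules: B by booking route, A by a code that the user must remember to bring. Take a person first allocated to A who later meets version B, books in it and attends. That visit enters the B total, and the A total loses it. The reverse sequence does not cancel this, because a person first given B who later sees A can still book through B and stay in the B count.

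Ordinary crossover dilutes a treatment difference. Counting by route can instead create a difference where none exists, in the primary outcome and in the direction that the investigators expect. In addition, 1000 allocations would stand for fewer than 1000 people.

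**Working it through.** **The plan's own figures.** Sample size states that if "approximately half of the users in Group A attend an appointment, we can detect a 20% change in the appointment rate", and then "With a 30% attended appointments rate in Group A, we still have power to detect a 30% difference between the groups", each "with beta = 0,80 and alpha = 0,05". I read 0.80 as power, alpha as two-sided, the changes as relative and the arms as 500 each. The formula is n per arm = [1.960·√(2·p̄·q̄) + 0.842·√(p₁q₁ + p₂q₂)]² / (p₂ − p₁)².

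- 50% v 60%: 388 per arm needed; power with 500 is 0.89.
- 30% v 39%: 437 per arm needed; power with 500 is 0.85.

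Both statements are met with some margin, so the sample size itself is not at fault here.

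**Spurious ratio under no effect.** The article gives no rate of repeat allocation, so two quantities are assumed:

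- d = share of attenders drawn on two devices, with independent 1:1 draws. A quarter get A twice, a quarter get B twice and half get both.
- p = chance that an attender drawn to both arms is scored in B.

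B share = 0.5(1 − d) + d(0.25 + 0.5p), and B/A ratio = share / (1 − share).

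| d | p | B share | B/A ratio |
|---|---|---|---|
| 10% | 100% | 0.450 + 0.075 = 0.525 | 1.11 |
| 20% | 100% | 0.400 + 0.150 = 0.550 | 1.22 |
| 40% | 100% | 0.300 + 0.300 = 0.600 | 1.50 |
| 20% | 75% | 0.400 + 0.125 = 0.525 | 1.11 |
| 20% | 50% | 0.400 + 0.100 = 0.500 | 1.00 |

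Even at p = 100%, only d/4 of attenders (5% at d = 20%) are counted in the wrong arm. Below p = 50% the error would favour A.

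**Chance of a false finding for B.** Take 500 first-allocated persons per arm and the same attendance rate π in both. Let r be the share of persons drawn a second time, and let everyone who saw B be scored in B. Expected attendances are 500π(1 − r/2) in A and 500π(1 + r/2) in B. The test is a two-sided comparison of proportions; its nominal rate in this tail is 2.5%.

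| r | π = 50%: A v B | false finding | π = 30%: A v B | false finding |
|---|---|---|---|---|
| 5% | 243.75 v 256.25 | 12% | 146.25 v 153.75 | 7% |
| 10% | 237.5 v 262.5 | 35% | 142.5 v 157.5 | 18% |
| 20% | 225 v 275 | 89% | 135 v 165 | 54% |

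If only half of the A-to-B switchers are scored in B (the p = 75% case), r = 20% gives about 35% and 18%.

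**Persons behind the denominator.** If 20% of persons hold one extra allocation, 1000 allocations represent 1000 / 1.2 = 833 persons.

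**The case against.** A reader might infer that repeat randomisation certainly happens and that every control user who later lands in B becomes a B attendance. The article supports neither reading.

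- Repeat allocation is possible, not shown. Secondary outcomes tracks new and returning visitors within each group, which suggests some memory of group on a device. How an allocation is stored is technical detail that an article may leave to the full protocol.
- Landing in B is not enough. Only a visit booked through the system and attended counts for B. A person who attends with a control code goes into the A grid. Booking by phone, described in Background, remains open, and the sample size presumes that many control users attend.
- Statistical methods speaks of attended visits with a randomisation code, compared between users of the two groups. This points to attribution by code as well as by route.
- Staff see cell phone numbers, so repeat bookers might be noticed.
- The 1.22 is a worst case; it needs both d = 20% and p = 100%.

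All of this stands and limits the size of the claim. It does not remove the claim. Memory on one device does not join two devices. Nothing says that a phone number is matched to an earlier allocation. The counting of B by route is stated outright in Primary outcome and is not a detail left out. That unequal counting would matter even without second devices; repeat allocation is one way in which it can turn into bias.

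**Conclusion.** The concern holds in a limited form. As described, one person can receive more than one allocation, and the counting rule lets a first-allocated control attender be recorded in Group B, or counted twice if both codes are shown. This can favour B. Whether it does, and by how much, cannot be settled from the article. At an assumed 20% of attenders drawn on two devices, the spurious ratio runs from 1.00 to 1.22 as the share of dual-allocated attenders scored in B runs from 50% to 100%. Only the upper end matches the 20% change that the trial is sized to detect. Both shares are assumptions. The point merits a change because the remedy is cheap and acts on the primary outcome; it is not evidence that the trial's result would be wrong.

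**What to change.** 1. Amend Primary outcome so that each attender is counted once, under the first allocation, whatever the booking route.
2. Add to the clinic grid, for both groups, a question on whether the person used the app on another device and which version or code came first.
3. Offer an optional prior-code field on the consent screen that restores the version first allocated.
4. Report how many attenders saw both versions, with a sensitivity analysis that assigns all of them to A and then all to B. Do not exclude them: seeing both versions happens after randomisation and is known only for attenders, so no matching denominator exists.
5. In Randomisation, state the unit of allocation and how it persists, and describe denominators as allocations, not persons.

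**Cost.** One optional screen field, one grid question and a short text change. The remedy relies on recall or a kept code, and users who skipped the symptom checker may have no code. Counting by first allocation also lets any real crossover dilute a true effect. With r = 20%, power for 50% v 60% falls from 0.89 to 0.82 if only A users cross over, and to 0.72 if both groups do. For 30% v 39% it falls from 0.85 to 0.77 and 0.67. Restoring the first version through the code field would reduce that loss.
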